**Abstract**

**Introduction:** In many low- and middle-income countries, community health volunteers (CHVs) are employed as a key element of the public health system in rural areas with poor accessibility. However, few studies have assessed the effectiveness of CHVs in improving child health in sub-Saharan Africa through randomized controlled trials. The present study aims to measure the impact of health promotion and case management implemented by CHVs on the health of under-5 children in Ghana.

**Methods and analysis:** This study presents the protocol of a cluster-randomized controlled trial assessing the impacts of CHVs, in which the community was used as the randomization unit. A phase-in design will be adopted, and the intervention arm will be implemented in the intervention arm during the first phase and in the control arm during the second phase. The key intervention is the deployment of CHVs, who provide health education, provide oral rehydration solutions and zinc tablets to children with diarrhea, and diagnose malaria using a thermometer and a rapid diagnostic test kit during home visits. The primary endpoints of the study are the prevalence of diarrhea and fever/malaria in children under 5 years of age, as well as the proportion of affected children receiving case management for diarrhea and malaria. The first and second rounds of household surveys to collect data will be conducted in the first phase, and the final round will be conducted during the second phase.

**Discussion:** With growing attention paid to the roles of CHVs as an essential part of the community health system in low-income countries, this study will contribute valuable information to the body of knowledge on the effects of CHVs.

**Ethics:** The study was approved by the Ghana Health Service Ethics Review Committee under the Ministry of Health, Republic of Ghana on July first, 2015.

**Trial registration number:** ISRCTN49236178. (June 16^th^, 2015)

**Keywords**

Community health workers, Community health systems, Diarrhea, Malaria, Child Health, Ghana

**Introduction**

Despite the substantial progress made between 1995 and 2015, over half of the deaths in children under 5 years of age in sub-Saharan Africa are still caused by malaria, diarrhea and pneumonia.^1^ Malaria alone caused 306,000 deaths among under-5 children in 2015 globally, including 292,000 deaths in sub-Saharan Africa.^2^ Diarrhea, largely due to the lack of safe water, sanitation and hygiene, killed 578,000 children in 2013, accounting for 9.2% of under-5 child deaths worldwide.^3^

Of the 62,000 deaths among Ghanaian children under 5 years of age in 2013, the majority were caused by malaria (20%), acute respiratory infections (13%), and diarrhea (8%).^4^ While other infectious diseases, such as HIV/AIDS and measles, have significantly decreased over the last decade in Ghana, diarrhea-specific child mortality has stagnated and malaria-specific deaths have decreased only by one percentage during the same period.^4^

Globally, given the limited human resources in the health sector, a community-based approach has been promoted as a cost-effective and pro-poor intervention to improve the accessibility of health care.^5, 6^ Community health workers (CHWs) are often employed as a key element of the community-based approach to the rural population of low- and middle-income countries.^7^ CHWs, in general, are defined as the non-professional lay health workers who are originally from the community and equipped with training and incentives to provide promotional, preventive, or curative health care services to the community members.^8-10^ They are known by various names in different settings, depending on the type of services offered, the compensation scheme, and the level of integration with the formal health system. For instance, Nigeria administers a village health worker program in which they are allowed to perform promotional work only, whereas health extension workers in Ethiopia are allowed to offer curative services for major illnesses. Lady health workers in Pakistan are paid as government employees, whereas a community health worker program in Tanzania operates based on volunteerism without regular payments.^11^

In Ghana, the Community-based Health Planning and Services (CHPS) initiative was adopted in 1999 as a national policy establishing a community health system to improve the accessibility and affordability of health care for residents in the remote areas.^6^ A distinctive feature of the CHPS system is the requirement of strong community engagement and participation. Community health nurses (CHNs) and community health volunteers (CHVs) are considered to be CHWs in the Ghanaian CHPS system. CHNs are formally trained for 2 years, bear the main responsibility for community health management within the formal governmental apparatus, and are on the government payroll. In contrast, CHVs are trained for a week and voluntarily support the outreach activities of CHNs and community participation, and are not paid by the government. Since community participation is a key aspect of the mechanism of the CHPS system, the role of CHV is as much critical as that of CHNs.^6, 12^

A number of studies have demonstrated that community-based health systems, particularly those involving CHWs, have led to improved access to maternal healthcare services^13-15^, modern contraception^16, 17^, and neonatal care among the poor.^18-22^ However, recently only few studies have investigated the impact of interventions made by CHWs on childhood illness in sub-Saharan Africa, using randomized controlled trials (RCTs).^23-26^ Moreover, many previous studies^27-31^ have evaluated the effect of CHWs only with the curative treatment while only one^26^ testing the effect with the preventive roles with RCT. A recent Cochrane systematic review evaluated 10 trials investigating the impact of CHWs with the expanded roles including prescription of anti-malarial drugs on the health of African children.^32^ Eight of them demonstrated the prescription of the drugs by CHWs without confirmation despite the World Health Organization’s recommendation to perform malaria diagnostic testing on all suspected malaria cases before administering treatment since 2010.^2^ To our knowledge, only one study published using RCT so far has tested the impact of CHWs in diarrhea management without provision of antibiotics while many others include the intervention with antibiotic prescription.^26^

Therefore, there is need for research testing the impact of CHWs, specifically regarding the promotive and preventive roles in major childhood illnesses in sub-Saharan Africa.

The study aims to measure the impact of CHVs on reducing childhood illnesses, especially malaria and diarrhea, in Ghana, which is one of the countries that has implemented a CHW program. We plan to explore the impact of CHVs, especially with regard to their role in the provision of health promotion, first-aid management for diarrhea oral rehydration solution (ORS) and zinc tablet, early diagnosis of malaria using rapid diagnostic tests (RDTs), and referrals for further treatment.

**Methods**

***Study setting***

The Ketu South district is one of the 25 administrative districts in the Volta Region, located in the southeastern corner of Ghana (See Figure 1). The Ketu South district is a relatively low land area, with altitudes ranging from less than 15 meters at the coast to 66 meters inland. The 2010 Population and Housing Census recorded a total population of 160,756, with 52.9% of the population consisting of females. The projected population for the district for 2015 based on an annual growth rate of 2.5% is 181,881, with 36,376 children under 5 years of age. The people of Ketu South are the Ewe tribe, which inhabits some parts of Togo, Benin, and the Volta Region of Ghana. They are a patrilineal society governed by a hierarchical, centralized authority. The district is culturally homogenous, with negligible variations. According to the 2010 Population and Housing Census, Christianity accounts for 59.0% of the total population, followed by traditional religion (27.9%) and Islam (3.5%). The people living in the district are predominantly fishermen, fish mongers, petty traders, and weavers of *kente* (a specific type of silk and cotton fabric that originated in the Ashanti Empire), with a few government workers interspersed among the population.

Figure 1. Study area.

| [figure not shown] |
| --- |

***Study design***

In the study, the community was taken as the randomization unit, because we expected that CHV activation will impact disease prevention and treatment among households within a given community, which is where people interact with one another most closely. All interventions related to CHV activation will be performed at the level of each community. A phase-in design will be used for the study. CHVs will be activated in the intervention arm during the first phase, and a comparable intervention will be performed in the control arm during the second phase.

The study was approved by the Ghana Health Service Ethics Review Committee under the Ministry of Health, Republic of Ghana (Ethics approval ID: GHS-ERC:07/01/15), and registered as an international standardized RCT on June 16, 2015 (ISRCTN49236178/ http://www.isrctn.com/ISRCTN49236178).

***Primary endpoint***

This study aims to assess the effect of CHVs on multiple child health outcomes. The primary endpoints of the study are the prevalence of diarrhea and fever/malaria among children under 5 years of age, and the proportion of children receiving case management for diarrhea and malaria. We plan to use the 14-day prevalence of reported diarrhea and the 14-day prevalence of fever/malaria in the household as indicated in caregiver’s reports.

For the case management for diarrhea, we will investigate whether a child with diarrhea has been administered ORS. For malaria, we will measure whether a child with malaria symptoms was tested using an RDT kit and whether he or she was referred to a health facility if diagnosed with malaria.

The survey will be conducted three times at the household level: the first and second round will be carried out in the first phase, and the final round will be carried out in the second phase.

Diarrheal is defined as 3 or more instances of watery stools within 24 hours over the last 14 days. Febrile episodes will be assessed as a proxy indicator of malarial prevalence based on caregiver reports.

The main outcomes and indicators are presented in Table 1.

Table 1. Main outcomes and indicators.

| **Indicator (%)** (Denominators are within the respondents of the household survey) | | |
| --- | --- | --- |
| Use of ORS among under-5 children with diarrhea | Numerator | Number of U5C^1^ who took ORS^2^ when experiencing diarrhea over the past 14 days |
|  | Denominator | Number of U5C who experienced diarrhea in the past 14 days |
| Prevalence of diarrhea in under-5 children | Numerator | Number of U5C who experienced diarrhea in the past 14 days |
|  | Denominator | Number of U5C |
| Diagnosis rate of malaria in under-5 children using an RDT | Numerator | U5C diagnosed with RDT for malaria in the last two weeks |
|  | Denominator | U5C who have complained of fever in the last two weeks |
| Malaria incidence in under-5 children | Numerator | U5C who have complained of fever in the last two weeks |
|  | Denominator | Number of U5C |

^1^ U5C, under-5 children; ^2^ ORS, oral rehydration solution

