**DISCUSSION**

This study seeks to assess the effects of CHVs on the health gains of children under 5 years of age. We thus rigorously applied a randomization process after calculating adequate cluster and household sample sizes.

In this study, we place an emphasis on the preventive role of CHVs in child health. The role of CHVs is to provide education about hand-washing, breastfeeding, the utilization of insecticide-treated nets, ORS treatment and rapid malaria tests, as well as making referrals for sick children to health facilities. We expect the health education using key messages during home visit will facilitate their function for disease prevention. Considering the context of resource-poor settings, the public health implications of the preventive role of CHVs is not trivial.

Previous studies did not describe the nature of CHV training or the availability of further education after the initial course. In this trial, CHVs are trained one week at the start of the project and regular training will be provided on a monthly basis by CHOs and CHNs.

We performed a pre- and post-test right before and after the CHV training. If we found a CHV not achieving a score of 80 out of 100, we retrained him or her. To standardize the regular training, standard operating procedure on the implementation of monthly meetings will be provided to the supervisors of the CHVs and it includes the guidance on the training. The regular training will be conducted based on the topics and messages from the home visit booklet that CHVs were provided with to facilitate their home visit education. Also, the monitoring team, composed of the district health directorate members and the project manager and staff, who oversee the monthly meeting and training activities of all CHVs, will coordinate the content and quality of regular training through active review and discussion.

The intervention is not restricted to health education. According to the operational definition of this trial, the key intervention is to help CHVs perform their duties, which mainly involve visiting at least 20 households each month to deliver key messages and provide basic health services established by the policy such as malaria diagnosis and ORS provision.

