One of the limitations of this trial is that malaria cases are not being confirmed using laboratory tests. We will measure fever reported by a caregiver as a proxy indicator of malaria prevalence in both arms of the trial. Although RDTs will be used to test for malaria in children with a fever, this will only be the case for households within the intervention arm since the testing will be conducted by CHVs. Despite its seasonal variance, fever, as the primary manifestation of malaria in young children, can be utilized as an indicator of malaria prevalence, although some source has suggested that it must be interpreted with caution [36].

The project team must start recruiting CHVs in control arm during the second phase and also reached an agreement with the local governments to commence CHV activation without any further delay right after the first phase regardless of any pronounced effects on children. If we have to implement CHV activation in the control arm, we cannot maintain two different arms with and without intervention, which means we cannot compare the outcomes of the intervention during this phase. Hence, we ruled out an optimization phase. We thus cannot consider an optimization phase for this trial although we think optimization is important.

Due to the absence of demographic data for the study district, we used estimated population figures for each community derived by the officials of the Ghana Health Service. However, during the baseline survey we found discrepancies between the estimated and actual number of households in communities, and these figures were adjusted during the sampling process in some communities. Although a pre-survey listing the households in each community is recommended to enhance the accuracy of household sampling, budgetary constraints prevented us from carrying out such a survey.

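### The referral component of the primary malaria endpoint is conditional on a diagnosis that the intervention itself produces, and it records a referral issued, not care reached

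*Protocol*

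**What the plan says.** The Protocol's Primary endpoint section lists among the primary endpoints "the proportion of children receiving case management for diarrhea and malaria". For malaria it gives two components. The first is "whether a child with malaria symptoms was tested using an RDT kit". The second applies only to some of those children: "whether he or she was referred to a health facility if diagnosed with malaria".

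Table 1, which that section presents as the list of main outcomes and indicators, covers only the first. Its numerator is "U5C diagnosed with RDT for malaria in the last two weeks" and its denominator is all under-5 children with fever in that period. Table 1 has no row for referral or for attendance at a facility, and the sections on intermediate and process indicators add none.

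Three other places bear on how the referral clause would work:

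- The limitations text in the Discussion says of rapid diagnostic test (RDT) use that "this will only be the case for households within the intervention arm since the testing will be conducted by CHVs". It draws the consequence for measuring malaria prevalence, not for the referral component.
- The closing paragraph of the Introduction describes the CHV role as "early diagnosis of malaria using rapid diagnostic tests (RDTs), and referrals for further treatment". Referral is thus a step towards treatment given elsewhere.
- Key intervention and Table 3 list oral rehydration solution, zinc, RDT kits and a thermometer among what CHVs carry or use. No antimalarial drug is listed.

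**The concern.** A between-arm comparison of proportions needs a denominator that the intervention does not reshape and an event that means the same thing in both arms. The referral clause is weak on both counts.

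CHV home testing creates diagnoses in one arm that would not otherwise exist. The diagnosed children in that arm will largely be those found at home visits. In the control arm they will be those who reached a test by some other route. The data analysis section plans intention-to-treat, but this does not help: each child is analysed in the assigned arm, yet who enters the denominator still depends on the arm.

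The event also stops one step short. CHVs are not described as giving antimalarial treatment, so any benefit from a malaria diagnosis depends on the child reaching a facility. A referral that the family does not follow counts the same as one that it does. A difference in the referral proportion is compatible with more, the same or fewer febrile children being seen at a facility. A reader of the results could take it as evidence of better care when it does not measure that.

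**Working it through.** The defect is one of definition. The arithmetic only shows how much of the febrile population the clause leaves out.

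**Inputs (Protocol, Table 2, round 1, last-born child).** Febrile: 294 intervention, 337 control. Malaria test when febrile: 55 intervention, 57 control.

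**Reproducing the printed percentages.** Control: 57/337 = 16.9%, as printed. Intervention: 55/294 = 18.7%, against a printed 17.7%. That mismatch is a separate matter. With either value, more than 80% were untested.

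**Share outside the measure before any test result is applied.** Intervention communities: 1 − 55/294 = 81.3%. Control communities: 1 − 57/337 = 83.1%. This takes a diagnosis to require a test, which the text does not say outright. Both arms were without CHVs at round 1, so the figures describe the situation without the intervention. They are a reasonable guide to the later control arm and not to the later intervention arm, where testing is meant to rise.

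**How the denominators could diverge (assumptions, for illustration).** Let t be the share of febrile children tested and p the share of tests that are positive. The share of febrile children who enter the denominator is t × p. The Protocol gives neither p nor the t expected with CHVs. Take p from 20% to 80%, the same in both arms:

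- Control, with t held at its round-1 value of 0.169: 0.169 × 0.2 = 3% to 0.169 × 0.8 = 14%.
- Intervention, with t from 0.3 to 0.8: 0.3 × 0.2 = 6% to 0.8 × 0.8 = 64%.

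At t = 0.5 and p = 0.5 the shares are 25% of febrile children in the intervention arm and 0.169 × 0.5 = 8% in the control arm. The gap comes from testing alone, with no difference in how any diagnosed child is handled.

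**The event.** Set the endpoint clause beside the Introduction's aim. The aim is further treatment; the endpoint counts the referral. Nothing in Table 1 or the indicator sections records whether the child arrived.

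**The case against.** **Table 1 already has a sound malaria indicator.** Its RDT row uses all febrile children and is defined the same way in both arms. This stands, and it narrows the point to the referral clause in the prose. The clause is still stated as part of the primary endpoint, and leaving it out of Table 1 leaves it undefined.

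**The control arm's test site and scoring are not stated.** A reader might infer that control children are diagnosed at facilities, score as not referred, and that the endpoint therefore favours the intervention by construction. The Protocol gives neither the site nor a scoring rule. If they are diagnosed at facilities, referral to one has little meaning for them, but that is conditional. The comparability problem does not depend on it.

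**The measure and the role need not match.** A reader might see a contradiction with the Discussion, which describes CHVs "making referrals for sick children to health facilities". There is none: an endpoint may be narrower than the role it samples, and nothing says that test-negative children go unreferred.

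**Care seeking may be captured elsewhere.** The Discussion lists changes in health-seeking behaviour among the process data. So the documents do not support saying that reduced attendance could not be detected at all. The item is undefined, however, and is not tied to fever or to test result.

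**Harm to test-negative children is not evidenced.** A reader might build such a case on the Introduction's figures of 20% of under-5 deaths from malaria and 13% from acute respiratory infection. Those are shares of deaths and say nothing about risk after a negative test.

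**The round-1 counts cannot size the later denominators.** Correct. Applying an assumed positivity to 55 and 57 and reading the result as follow-up numbers per arm is not supported.

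**Conclusion.** The point holds for the referral clause only. As written, that part of a primary endpoint compares subsets formed after randomisation that differ in kind between arms, and it counts a referral issued. It cannot be validly compared between arms, and it does not show whether febrile children reached care.

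The size that the documents support is limited: without CHVs, over 80% of febrile children (81.3% and 83.1% at round 1) would probably be outside the measure. This assumes that a diagnosis needs a test and that last-born children represent under-5 children generally. The control denominator is small and selected, but not empty. The direction of any bias cannot be fixed from the documents, because it depends on where control children are tested and how they are scored.

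The Table 1 RDT row, the prevalence endpoints and the diarrhoea endpoints are untouched by this point.

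**What to change.** 1. In the Primary endpoint section, remove the diagnosis-conditional referral clause from the between-arm primary comparison.
2. Add a row to Table 1. Numerator: children with fever in the last 14 days whose caregiver reports that they were seen at a health facility for that episode. Denominator: all children with fever in the last 14 days. Use the same question in both arms.
3. Read this row alongside the existing RDT row, since home testing may change who needs to attend. Neither row alone is a neutral measure of quality.
4. Keep CHV referral issued and referral completed as intervention-arm process indicators, reported separately by RDT result.
5. Define the health-seeking item in the Discussion by reference to the new row.

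One limitation remains. Fever is itself an outcome that the intervention aims to reduce, so the febrile group is also formed after randomisation. It is, however, ascertained by the same caregiver report in both arms, and Table 1 already uses it as a denominator.

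The cost is one or two extra caregiver questions in survey rounds already planned for both arms. The first-round survey and randomisation are complete and no round-1 attendance value is shown, so there may be no baseline to adjust for; the randomised comparison does not require one. Because the trial is registered and under way, this is a change to one component of a primary endpoint. It needs to be documented as such, with its date and reason.
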